**Figure 1 f1:**
[figure not shown]
Flow diagram illustrating study methods.

**Figure 2 f2:**
[figure not shown]
A detailed description of the assessments measures, *assessment is optional at follow-ups. Standard Protocol Items: Recommendations for Interventional Trials (SPIRIT) schedule.

### Recruitment and procedures

Patients diagnosed with stage I-III breast cancer will be recruited from Health Care Global (HCG) Cancer Hospital in Bengaluru, India. Initially, healthcare providers identify the potentially eligible participants and orient the study in brief to them. Patients are then contacted by study staff to confer their eligibility and receive informed consent to participate in the study. Patients are also recruited *via* posters displayed in waiting lobbies and examination chambers, advertisements on the hospital’s webpage, and word-of-mouth promotion. Women asking for more information about the study are encouraged to contact research staff over the phone or by email.

### Participant eligibility

#### Inclusion criteria

Women who meet the following criteria will be eligible to participate in the study: (1) 18–60 years of age; (2) diagnosed with stage I-III (i.e., non-metastatic) breast cancer; (3) scheduled to receive at least six cycles of adjuvant or neoadjuvant chemotherapy; (4) can speak and comprehend English (in order to perform neuropsychological test battery) and; (5) have support from their medical oncologist to participate in the yoga intervention. They must also score ≥23 on the Montreal Cognitive Assessment (MoCA) (42) and ≥ 55 on the LVEF of echocardiography before randomization.

#### Exclusion criteria

Patients who match the following exclusion criteria will not be eligible to participate in the study: (1) prior exposure to chemotherapy or radiotherapy; (2) during screening, a score of ≤23 on the Montreal Cognitive Assessment (MOCA) scale (as a score less than 23 is considered cognitively impaired) (3) diagnosis of neurological disorders such as epilepsy, Parkinson’s disease, neurodegenerative disorders; (4) severe anxiety or mood disorder (e.g., major depressive disorder) diagnosed within the past year; (5) traumatic brain injury or concussion with persisting symptoms (e.g., dizziness, headaches, lack of attention) at the time of screening; (6) above 60 years of age (as cognitive abilities often decline with an increase in age) (7) substance use disorder (e.g., alcohol, narcotics); (8) regular participation in an active behavioral intervention/yoga in last six months. (9) Injuries or illnesses (e.g., orthopedic injury, acute arthritis) that prevent stretching while practising asanas.

#### Added inclusion/exclusion criteria for MRI/fMRI

During the initial screening phase, eligible participants will be asked if they would also be interested in undergoing an additional optional MRI/fMRI evaluation. The MRI/fMRI is performed at three different time points: baseline (before chemotherapy), post-chemotherapy, and 1-year post-baseline. The additional exclusion criteria listed below apply to the MRI/fMIR evaluation: (1) Left-handedness (owing to lateralization of language in right-handed people); (2) Metal implants (such as pacemakers) or metal dental work other than fillings (which are not compatible with MRI/fMRI); (3) claustrophobic; (4) current breast tissue expanders (since these are not MRI/fMRI compatible), and; (6) Lower back ache that would prevent lying motionless for an hour.

#### Screening procedure and informed consent

Initial screening will be performed to ensure that participants meet the primary eligibility requirements. If women are determined to be eligible, MOCA and 2D echocardiography (for evaluating Left Ventricular Ejection Fraction-LVEF) will be administered. MOCA is a quick 30-point test that will be used to assess cognitive deficits, and LVEF is a marker for cardiac health. MoCA and LVEF are administered prior to any study-related activity to establish women’s final eligibility. Patients scoring ≥ 24 on MoCA and ≥ 55 on the LVEF are invited to read and sign the informed consent form.

#### Randomization

Subjects satisfying the selection criteria and consenting to participate will be assessed at baseline with subjective and objective measures prior to starting chemotherapy. Randomization will then be done with an allocation ratio of 1:1 into the yoga (YI) or control (SC) group following the baseline assessment using computer generated random numbers. Allocation concealment will be done by using opaque envelopes with group assignments by personnel not involved in the study. The order of enrolment will be verified using hospital records.

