#### Sample size estimation

Considering the effect size observed, in an earlier study by Vadiraja & Rao et al. (31), with improvement in cognitive function domain of EORTC Qol-C30 between yoga and control group as 0.49 with a 95% confidence interval and 80% power, we need a sample size of 67 subjects in each arm. If attrition is within 20% through the course of the intervention, 75 subjects will be recruited in each arm. Therefore 150 consenting subjects will be randomized into each group (yoga, n=75, and controls, n=75) with an allocation ratio of 1:1. The analyses would consider a two-tailed probability of p < 0.05 as significant. This ensures that a statistical type I error (probability of detecting a false positive) is less than 5%. The analyses will involve ANCOVA using the respective baseline measure as a covariate.

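### Treatment setting (adjuvant or neoadjuvant), known before randomisation, is not among the stated covariates; adding it is a small efficiency gain, not the repair of an error

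*Protocol article*

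**What the plan says.** The Inclusion criteria admit women "scheduled to receive at least six cycles of adjuvant or neoadjuvant chemotherapy", and the abstract describes the same mix. The share of each group is not given.

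The Randomization section states: "Randomization will then be done with an allocation ratio of 1:1". This happens after the baseline assessment, "using computer generated random numbers", with opaque envelopes for concealment. It names no strata, blocks or minimisation factors.

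Covariates are described in two places:
- Sample size estimation: "The analyses will involve ANCOVA using the respective baseline measure as a covariate".
- Statistical analyses: factors usually tied to dropout enter every analysis as covariates. Age and length of chemotherapy are given as examples, so the list is open.

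Treatment setting appears in none of these three sections.

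**The concern.** By the meaning of the terms, adjuvant women reach the pre-chemotherapy baseline after surgery, and neoadjuvant women have surgery after chemotherapy. The article allows for this mix. The exclusion criteria rule out earlier chemotherapy or radiotherapy but not earlier surgery, and the MRI criteria exclude women with tissue expanders in place. The follow-up visits, 16 weeks after chemotherapy and one year after baseline, therefore fall at different distances from surgery in the two settings.

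The article itself links yoga to post-operative recovery (Background), and stress and mood to cognition (Discussion). A relation between setting and the outcomes is thus plausible. The baseline score cannot account for surgery that happens later.

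A pre-randomisation factor related to the outcome is worth having in the model: it reduces residual variance and takes the effect of any chance imbalance in that factor out of the estimate. At stake is a little precision, and an easy answer if the arms happen to differ in their mix of settings.

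**Working it through.** **Inputs from the article (Sample size estimation).** Standardised effect 0.49, so SD = 1; 80% power; two-sided 0.05; 67 evaluable and 75 recruited per arm.

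**Assumed, because the article gives no figures.** Setting effect b = 0.2 to 0.5 SD; neoadjuvant share p = 30% to 50%.

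**1. The plan's own figure.** n per arm = 2 × (1.960 + 0.842)² / 0.49² = 65.4, rounded up to 66. The t-test version gives 66.35, rounded up to 67. The stated 67 reproduces. Power at 67 per arm is 81.0% (normal approximation) or 80.4% (t-test).

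**2. Chance imbalance under simple randomisation, 75 per arm.** The SD of the difference in neoadjuvant share is √(2p(1−p)/75).
- p = 0.5: SD 0.082; chance of a gap above 10 points 22%, above 15 points 6.6%.
- p = 0.3: SD 0.075; chances 18% and 4.5%.

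Without adjustment, a 10-point gap moves the estimate by 0.10 × b = 0.02 to 0.05 SD, against a target of 0.49. A 15-point gap moves it by 0.03 to 0.075 SD.

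**3. Validity if setting is ignored.** In 40,000 simulated trials for each effect size (67 per arm, p = 0.5, no adjustment), type I error was 5.1% at b = 0.3 and 4.8% at b = 0.5. The mean estimate was 0.49 and power about 81%. Nothing is biased or inflated.

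**4. Gain from adjusting, before baseline adjustment.** R² = b²p(1−p); residual SD = √(1−R²).
- Lowest: 0.2² × 0.3 × 0.7 = 0.0084, so 0.8%. Required n is 65 per arm; power at 67 is 81.3%.
- Highest: 0.5² × 0.5 × 0.5 = 0.0625, so 6.3%. Required n is 62 per arm; power at 67 is 83.4%.

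The gain is 0.3 to 2.4 power points, and required n falls from 66 to between 62 and 65 per arm. With 60 evaluable per arm (75 × 0.8, the article's 20% attrition limit), power goes from 76.5% to between 76.9% and 79.2%.

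**5. Gain when the baseline score is already in the model.** Illustration: setting shifts baseline and outcome equally by 0.5 SD, within-setting correlation 0.5, within-setting variance 1, equal split.
- Total variance: 1 + 0.0625 = 1.0625.
- Covariance of baseline and outcome: 0.5 + 0.0625 = 0.5625.
- Residual variance with baseline only: 1.0625 − 0.5625²/1.0625 = 0.765.
- Residual variance with baseline and setting: 1 − 0.5² = 0.750.

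The reduction is about 2%, worth about 3 women of 150.

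**The case against.** The case against raising this at all is substantial, and much of it stands.

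- A reader might infer that the analysis adjusts for the baseline score alone. It does not: the Statistical analyses section adds dropout-related covariates to every analysis, through an open list.
- A reader might infer that the randomisation is unstratified. The article is only silent. It condenses a fuller protocol, and strata may be set out there.
- A reader might call setting a known prognostic factor. Nothing in the article says that it predicts the cognitive score, so plausibly related is as far as one can go.
- A reader might think that chance imbalance biases the result. Under valid randomisation the standard error and p-value already allow for it, as the simulation shows.
- For the primary endpoint at the end of chemotherapy, much of any difference due to earlier surgery may already sit in the baseline score. The later visits, where setting has most room to matter, are ones the team undertakes only to try to analyse.

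What remains is narrow. The stated covariates are chosen for their link with dropout, and setting is not among the examples. Length of chemotherapy is no substitute: the same six-cycle minimum applies in both settings, and duration actually received would be a post-randomisation measure. If the full protocol does stratify by setting, that is a further reason to put it in the model.

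**Conclusion.** The point holds as a modest suggestion on efficiency. The article enrols both settings and names setting neither in the allocation nor among its covariates, although it is known beforehand for every woman. The plan is valid without it; there is no bias and no inflation of type I error to correct.

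The benefit is 0.3 to 2.4 power points at 67 per arm before baseline adjustment, and possibly only about 2% of residual variance after it. These figures rest on an assumed setting effect of 0.2 to 0.5 SD and an assumed neoadjuvant share of 30% to 50%. If setting is unrelated to the outcome, the gain is nil. The benefit is likeliest at the follow-up visits.

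**What to change.** Name treatment setting (adjuvant or neoadjuvant) as a prespecified covariate beside the baseline score in the primary model and the follow-up models. Fix this before unblinding, and preferably before the masked analysis begins, since the Blinding section places unblinding after the data have been analysed.

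The cost is one degree of freedom and a sentence in the analysis plan. Setting is part of an eligibility criterion, so it is known at screening; the team need only confirm that it is held in the trial database. The allocation list does not need to be redrawn: a gain of this size does not justify changing the randomisation procedure and the sealed envelopes during the trial.

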#### Blinding

Participants and study personnel will be naïve to group allocation since randomization occurs after baseline evaluations. Following randomization, a single-blind procedure is used so that the study staff who do the assessments and the statistician who looks at the data will be blinded to group allocation. All patient identifiers will be removed, and data will be analysed blindly. Unblinding will be done only after all data are analysed and entered into the database after completing the study. This would ensure unbiased analyses of the data.

#### Sample size estimation

Considering the effect size observed, in an earlier study by Vadiraja & Rao et al. (31), with improvement in cognitive function domain of EORTC Qol-C30 between yoga and control group as 0.49 with a 95% confidence interval and 80% power, we need a sample size of 67 subjects in each arm. If attrition is within 20% through the course of the intervention, 75 subjects will be recruited in each arm. Therefore 150 consenting subjects will be randomized into each group (yoga, n=75, and controls, n=75) with an allocation ratio of 1:1. The analyses would consider a two-tailed probability of p < 0.05 as significant. This ensures that a statistical type I error (probability of detecting a false positive) is less than 5%. The analyses will involve ANCOVA using the respective baseline measure as a covariate.

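### Recruiting 75 per arm does not cover the stated 20% attrition: 60 per arm would remain against the 67 required, and power would be about 76%, not 80%

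*Protocol article*

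**What the plan says.** All the figures stand together in the Protocol article, Sample size estimation.

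- **Effect and power:** the improvement in the EORTC QLQ-C30 cognitive domain is taken from an earlier study, "between yoga and control group as 0.49 with a 95% confidence interval and 80% power".
- **Significance level:** "The analyses would consider a two-tailed probability of p < 0.05 as significant".
- **Required number:** "we need a sample size of 67 subjects in each arm".
- **Attrition step:** "If attrition is within 20% through the course of the intervention, 75 subjects will be recruited in each arm".
- **Randomised number:** "Therefore 150 consenting subjects will be randomized into each group (yoga, n=75, and controls, n=75"), at 1:1.

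The section closes by naming ANCOVA with the baseline value as covariate. It gives no baseline-to-outcome correlation. No other section gives a different attrition rate or a reason why 75 per arm would be enough.

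**The concern.** The step from 67 to 75 is presented as the allowance for attrition of up to 20%, but 75 is only about 12% above 67 (75/67 = 1.119). Losing a fifth of 75 leaves fewer than 67. The required number, the attrition allowance, the recruitment target and the 80% power therefore cannot all hold.

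This bears on the primary outcome, the cognitive domain of the EORTC QLQ-C30. Anyone monitoring retention against the stated 20% would believe power was protected when losses between about 11% and 20% already take the trial below its own requirement. The article also lists adequate sample size as the first strength of the trial (Strength of the study).

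The sentence on the randomised number has a slip of its own: it places 150 subjects in each group, while its parenthesis gives 75 and 75.

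**Working it through.** **Inputs, all from Sample size estimation:** d = 0.49 (SD taken as 1), two-sided alpha 0.05, power 80%, 67 evaluable per arm, attrition up to 20%, 75 recruited per arm, 1:1 allocation.

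**1. Reproduce the 67.**
- Normal formula: n = 2 × [(1.960 + 0.842)/0.49]² = 65.4, so 66 per arm.
- Two-sample t-test (noncentral t): 66.35, so 67 per arm. Power at 67 is 80.4%.

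The stated 67 matches the t-test exactly, so its basis is an unadjusted two-group comparison.

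**2. Inflate for 20% attrition.**
- Correct: 67/(1 − 0.20) = 83.75, so 84 per arm and 168 in total.
- Common shortcut: 67 × 1.20 = 80.4, so 81 per arm.

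Neither gives 75. The shortfall against 84 is 9 per arm, 18 in total.

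**3. What 75 per arm does cover.**
- 1 − 67/75 = 10.7%, that is, 8 losses out of 75.
- 67/0.90 = 74.4, so 75 is the number that fits a 10% allowance.

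**4. Power at the stated 20%.**
- Evaluable: 75 × 0.80 = 60 per arm.
- Noncentrality: 0.49 × √(60/2) = 2.684.
- Normal approximation: Φ(2.684 − 1.960) = 76.5%.
- Noncentral t: 75.9%.
- Effect detectable with 80% power at 60 per arm: 0.516.

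**5. Power across the range of attrition (d = 0.49, t-test, unadjusted).**

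| Attrition | Evaluable per arm | Power |
|---|---|---|
| 0% | 75 | 84.6% |
| 5% | 71.25 | 82.8% |
| 10% | 67.5 | 80.7% |
| 15% | 63.75 | 78.4% |
| 20% | 60 | 75.9% |

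**6. Effect of baseline adjustment at 60 per arm.** The document gives no baseline-to-outcome correlation r, so r is an assumption here. I also assume that 0.49 is on the unadjusted SD scale. ANCOVA then multiplies the residual variance by 1 − r², and the effective effect size is 0.49/√(1 − r²).

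| r | Power |
|---|---|
| 0 | 75.9% |
| 0.2 | 77.5% |
| 0.3 | 79.7% |
| 0.4 | 82.8% |
| 0.5 | 86.7% |

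Power reaches 80% at r = 0.312.

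**The case against.** **The 20% is an upper bound.** The plan allows for attrition within 20% and does not predict 20%. Unadjusted power stays at or above 80% for losses up to about 10.7%, so 76% describes the worst case allowed. That is correct and should be said. But an attrition allowance has to hold over the range it names, and this one fails over nearly half of it.

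**The 76% is not the power of the named analysis.** The section specifies ANCOVA, and Statistical analyses adds intention to treat with covariates under missing at random. A correlation of about 0.31 would restore 80% at 60 per arm, so a real shortfall under ANCOVA is not proven. This stands as a caveat. However, the plan states no correlation and its 67 takes no credit for one. Whether 0.49 already reflects baseline adjustment cannot be told from the article. Intention to treat does not replace outcomes that were never observed. The Statistical analyses section also describes a repeated measures ANOVA, so it is not settled that ANCOVA is the primary test.

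**The significance threshold differs between sections.** Statistical analyses uses p ≤ 0.008 for the interaction, against 0.05 in the sample size section. That is a separate matter. It does mean that any restated power should name the level it refers to.

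**The loss is small.** Four points of power and a move from 0.49 to 0.516 are modest, and no estimate or test changes. This is fair as to size, but it does not reconcile the figures. The 150-per-group wording is clerical: the parenthesis makes the meaning clear, and it adds no weight.

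**Conclusion.** The point holds. The 67 per arm is right on its own assumptions, but 75 per arm does not follow from 67 and 20% by any usual inflation. It covers about 10.7% attrition, and the stated 20% would need 84 per arm. If the full 20% is lost, 60 per arm remain, with 75.9% power for 0.49 and a detectable effect of 0.516 at 80% power.

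These power figures rest on d = 0.49, two-sided alpha 0.05, equal losses in the two arms and an unadjusted comparison, which is the calculation that yields 67. The size of the shortfall depends on actual attrition and on any gain from baseline adjustment. The inconsistency between 67, 20% and 75 depends on neither.

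**What to change.** Restate the figures, with no change in enrolment. Any one of these would do:

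- **(a)** State that 75 per arm keeps 80% power for attrition up to about 10%. The sponsor should then be able to defend 10% as realistic, since nothing in the article supports it.
- **(b)** Keep the 20% allowance and state that power is then about 76% for an unadjusted comparison at two-sided 5%.
- **(c)** If the baseline-adjusted ANCOVA is the primary test, keep 20% and state the correlation assumed between baseline and end of chemotherapy, with its source. A value of at least about 0.31 gives 80% with 60 per arm, provided 0.49 is an unadjusted effect size.

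In the same edit, change the randomisation sentence to say 150 in total, 75 per group.

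The cost is wording only, plus a stated figure that becomes slightly less favourable under (a) or (b).

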### Integrated Yoga Therapy program (IYTP)

The IYTP intervention will be given to participants along with their chemotherapy. For those in the YI group, it starts up to a week before chemotherapy begins and lasts until chemotherapy ends. The intervention is based on earlier protocols employed by the study team for breast cancer patients and found to have good patient adherence (32, 39) that they could perform these practices 5 days/week during intensive chemotherapy treatment. **Table 1** summarizes the IYTP prescription. The intervention will consist of 14 - 24 weeks (five days a week) of hospital and home-based moderate yoga therapy sessions compared with standard care alone while patients undergo chemotherapy. The practices will be taught in the hospital by a trained yoga therapist during chemotherapy and supervised online for home practices. The initial one-week yoga session will be administered in person as a one-to-one session in the hospital setup between 9 AM to 10 AM. After the patient is discharged from the hospital post their first chemotherapy cycle, they will be advised to continue yoga practice at home between 7 AM to 9 AM with a documented video and an intervention brochure outlining the instructions and benefits of yoga. Subsequently, when they come to the hospital for their following chemotherapy cycles (once every 21 days throughout their six cycles of chemotherapy), they will be refreshed with in-person yoga sessions, where necessary refinements to their practices will be made. Also, Also, their performance in yoga will be graded using the “Yoga Performance Assessment” (YPA) scale, a tool devised by Swami Vivekananda Yoga Anusandhana Samsthana (SVYASA) and Advanced Centre for Yoga (NIMHANS) for recording patient compliance to yoga practices (43).

**Table 1 T1:** Showing the list of practices.

	Practice List	Time in minutes
**1.**	**Loosening Practices SukshmaVyayama (4 minutes)**	
1.a	Neck Forward & Backward bending	1
1.b	Neck Side Bending	1
1.c	Neck Rotation – Clockwise and Anti-Clockwise	2
**2**	**Breathing Practices (3 minutes)**	
2.a	Hands In & Out Breathing	1
2.b	Shoulder Stretch Breathing	1
2.c	Ankle Stretch Breathing	1
**3.**	**Yoga Postures or Asanas (7 minutes)**	
3.a	Tadasana (Mountain Pose)	1
3.b	Ardha Kati Chakrasana (Lateral Arc pose)	2
3.c	Padahastasana (Hand to foot pose)	1
3.d	Ardha Chakrasana (Standing Backward Bend or Half wheel pose)	1
3.e	Vrikshasana (Tree pose)	1
3.f	Utkatasana (with/without support) (Chair pose)	1
**4**	**Yogic Relaxation – Instant Relaxation Technique (3 minutes)**	
4.a	Bhujangasana Breathing (Cobra pose)	1
4.b	Shashankasana Breathing with Bhramari (Rabbit pose)	1
**5**	**Yogic Breathing (4 minutes)**	
**6**	**Kriya/Pranayama (4 minutes)**	
6.a	Slow phase Kapalabhati (Skull shinning Breath)	1
6.b	NadiShuddhi Pranayama (Alternate Nostril Breathing)	3
**7**	**Breath awareness (10 minutes)**	
**8**	**Yogic Relaxation – Quick Relaxation Technique (3 minutes)**	
	**Total**	**40 min**

Patients will undergo supervised yoga session for 18 weeks (5 days/week) at the oncology centre and home based. The intervention is tailored primarily to prevent chemobrain and cardiac dysfunction symptoms following chemotherapy.

The intervention comprises of asanas (postures), breathing exercises, pranayama (voluntarily regulated nostril breathing), mindfulness-based meditation, and imagery-based yogic relaxation techniques. We have primarily involved asanas that are balancing in nature as they are known to improve attention and memory with proven effects of stress reduction. Among pranayama (regulated nostril breathing), yogic breathing with breath-holding (Kumbhaka) after exhalation, Bramari (Humming bee sound) and Nadishuddi pranayama were involved. Kapalabhati is known to increase brain blood flow and improve cognition (44). These practices will be interspersed with Yogic relaxation techniques. All these practices were based on principles of enhancing attention, awareness, and relaxation to cope with stressful experiences faced by cancer patients during and after treatment.

Our yoga module encompasses balancing postures (Vrikshasana, Tadasana (centering awareness), padahastasana, ardha chakrasana, ardha kati chakrasana, bhujangasana and shashankasana with “m” kar chanting, followed by yogic breathing, kapalabhati, nadishuddhi and bramari pranayama. The literature review from yoga texts are appended as under.

The attentional cues facilitated by asanas would help in modulating attentional process involved in cognition and help modulate cognitive function and flexibility. Therefore asanas confer not only physical flexibility but also modulate cognitive flexibility. This is emphasised in the Patanjali yoga sutras in chapter 2, verse 48.

During pranayama, internalising the awareness of the breath, such as the motions of inhalation, exhalation, and the kumbhaka, will help calm down the mind and clear mind of all other distractions. This helps prepare the mind for concentration and attention, improving cognitive faculties.

Furthermore, these practices were shown to improve cognitive and cardiac functions in earlier studies conducted at the HCG cancer centre and various oncology centres across India (32, 45).

